# Protocol for the postoperative radiotherapy in N1 breast cancer patients (PORT-N1) trial, a prospective multicenter, randomized, controlled, non-inferiority trial of patients receiving breast-conserving surgery or mastectomy

**DOI:** 10.1186/s12885-022-10285-0

**Published:** 2022-11-16

**Keywords:** Adjuvant radiotherapy, Breast cancer, Lumpectomy, Mastectomy, pN1

## Abstract

**Background:**

Postoperative radiotherapy (PORT) could be useful for pN1 breast cancer patients who have undergone breast-conserving surgery (BCS) or mastectomy. However, the value of regional nodal irradiation (RNI) for BCS patients, and the indications for post-mastectomy radiotherapy (PMRT) for pN1 breast cancer mastectomy patients, have recently been challenged due to the absence of relevant trials in the era of modern systemic therapy. “PORT de-escalation” should be assessed in patients with pN1 breast cancer.

**Methods:**

The PORT-N1 trial is a multicenter, randomized, phase 3 clinical trial for patients with pN1 breast cancer that compares the outcomes of control [whole-breast irradiation (WBI) and RNI/PMRT] and experimental (WBI alone/no PMRT) groups. PORT-N1 aims to demonstrate non-inferiority of the experimental group by comparing 7-year disease-free survival rates with the control group. Female breast cancer patients with pT1-3 N1 status after BCS or mastectomy are eligible. Participants will be randomly assigned to the two groups in a 1:1 ratio. Randomization will be stratified by surgery type (BCS vs. mastectomy) and histologic subtype (triple-negative vs. non-triple-negative). In patients who receive mastectomy, dissection of ≥5 nodes is required when there is one positive node, and axillary lymph node dissection when there are two or three positive nodes. Patients receiving neoadjuvant chemotherapy are not eligible. RNI includes a “high-tangent” or wider irradiation field. This study will aim to recruit 1106 patients.

**Discussion:**

The PORT-N1 trial aims to verify that PORT de-escalation after BCS or mastectomy is safe for pN1 breast cancer patients in terms of oncologic outcomes and capable of reducing toxicity rates. This trial will provide information crucial for designing PORT de-escalation strategies for patients with pN1 breast cancer.

**Trial registration:**

This trial was registered at ClinicalTrials.gov (NCT05440149) on June 30, 2022.

## Background

Although surgery is the mainstay of definitive breast cancer treatment, postoperative radiotherapy (PORT) also plays an essential role. The two main types of radical surgery for breast cancer are breast-conserving surgery (BCS) and mastectomy. PORT is crucial in most patients who have undergone BCS: several randomized trials and meta-analyses showed that PORT reduces breast cancer recurrence and death [1, 2]. However, PORT is not always the best option for patients who received a mastectomy. Radiotherapy is recommended when the tumor is large (> 5 cm) or regional metastasis is confirmed during axillary surgery [3, 4]. These principles have informed breast cancer treatment for many years.

Systemic therapy is another essential component of breast cancer treatment, and has advanced greatly in recent years. Long-term hormonal therapy and ovarian suppression have been applied in patients with positive hormonal receptors to further decrease the risk of breast cancer recurrence [5, 6]. Trastuzumab is widely used in human epidermal growth factor receptor 2 (HER2)-positive breast cancer patients and significantly improves the prognosis [7]. High-risk HER2-positive breast cancer patients can also benefit from pertuzumab [8]. The addition of taxane to adjuvant chemotherapy has increased patient survival rates [9]. However, as the major clinical trials supporting PORT did not consider these advancements [10], it remains uncertain whether modern systemic therapy impacts the effectiveness of radiotherapy. With the increased application of systemic therapy, de-escalation of certain aspects of PORT may be feasible in selected patients, such as field size reduction or the omission of radiotherapy.

The PORT field is subject to debate. A larger radiation field is needed for patients at higher risk of regional metastasis; however, the extent of the field and factor necessitating a larger one have not been determined, especially in patients with 1–3 positive axillary lymph nodes. Some randomized trials have attempted to determine the effectiveness of regional nodal irradiation (RNI). In the MA.20 trial, which included breast cancer patients with high-risk pathologic features, RNI covered axillary, supraclavicular lymph node (SCL), and internal mammary lymph node (IMN) areas. The results showed benefits of RNI in terms of disease-free survival (DFS) [11]. In the European Organisation for Research and Treatment of Cancer (EORTC) 22922/10925 trial, irradiation of the IMN and medial SCL areas was performed, and breast cancer mortality was decreased [12]. The IMN was also irradiated in a French trial, but there was no survival benefit [13]. As extent of RNI was different between these randomized trials, indications for irradiation of specific nodes cannot be established [14]. Furthermore, the indications of RNI according to the number of positive lymph nodes in axillary surgery remain uncertain.

The current indications for PORT after mastectomy have been criticized. Although the Early Breast Cancer Trialists’ Collaborative Group meta-analysis confirmed a benefit of post-mastectomy radiotherapy (PMRT) for pN1 patients [15], this conclusion was based primarily on the results of two Danish trials criticized for their high rates of inadequate axillary surgery. In addition, more than two decades have passed since these results were reported, and the benefit of PORT may have lessened due to advances in breast cancer treatment [10]. Secondary analysis of the prospective data of pT1-2 N1 patients enrolled in the BIG 02-98 randomized trial of adjuvant chemotherapy revealed that PMRT slightly improved locoregional control, but not survival rates [16]. Thus, the role of PORT after mastectomy must be reevaluated based on more recent evidence.

Although several non-randomized series have provided insight into “PORT de-escalation” [17–19], oncologic safety has not been confirmed. If the oncologic safety of PORT de-escalation can be established, breast cancer patients may benefit from reduced toxicity and lower time and medical costs. Accordingly, the Korean Radiation Oncology Group (KROG) designed a multicenter clinical trial of PORT for patients with pN1 breast cancer: the Postoperative Radiotherapy in N1 Breast Cancer Patients (PORT-N1) trial. This trial aims to evaluate the feasibility of PORT de-escalation in pN1 breast cancer patients by establishing indications for RNI in patients receiving BCS, and for PMRT in patients receiving a mastectomy.

## Methods and design

### Study design

PORT-N1 is a prospective multicenter randomized controlled non-inferiority trial. The study design is illustrated in Fig. 1. Twenty-one academic centers in South Korea are participating in this trial. Participants with 1–3 positive lymph nodes (found during axillary surgery), who did not receive neoadjuvant systemic therapy and underwent BCS or mastectomy, were randomized in a 1:1 ratio to the control and experimental groups. Participants allocated to the control group who underwent BCS will undergo whole-breast irradiation (WBI) with RNI, while those who underwent mastectomy will undergo PMRT. Participants allocated to the experimental group will undergo WBI only if they underwent BCS. PMRT will not be performed in experimental group participants who underwent mastectomy. This trial is anticipated to run for 11 years, with a 4-year recruitment phase and 7-year follow-up. The first participant was recruited on July 19, 2022. Participant registration is expected to be completed in December 2026, and the final results will be available after 2033. This protocol was approved by the KROG and designated as KROG 22-05. This trial was registered at ClinicalTrials.gov (NCT05440149) on June 30, 2022.

**Fig. 1 Fig1:**
[figure not shown]
Schematic diagram of the design of the Postoperative Radiotherapy in N1 Breast Cancer Patients (PORT-N1) trial of patients receiving breast-conserving surgery (BCS) or mastectomy. CIN, cervical intraepithelial neoplasia; ECOG, Eastern Cooperative Oncology Group; ER, estrogen receptor; HER2, human epidermal growth factor receptor 2; PMRT, post-mastectomy radiotherapy; PR, progesterone receptor; TM, total mastectomy; RT, radiation therapy; TNBC, triple-negative breast cancer; WBI, whole-breast irradiation

### Eligibility criteria

The inclusion criteria are as follows: female patients aged ≥19 years living in South Korea available for long-term follow-up; receiving BCS or mastectomy for pathologically confirmed invasive breast cancer; 1–3 positive axillary lymph nodes (of any diameter) confirmed during the pathologic examination of a surgical specimen, with the additional requirements of ≥5 lymph nodes dissected in cases with 1 positive lymph node and axillary lymph node dissection in cases with 2–3 positive lymph nodes for mastectomy; adjuvant hormonal therapy scheduled for a positive estrogen or progesterone receptor; adjuvant HER2-targeted therapy scheduled for HER2-positive cancer; Eastern Cooperative Oncology Group (ECOG) performance status of 0–2; and provision of written informed consent.

The exclusion criteria are as follows: radiotherapy scheduled for palliative purposes; T4 disease revealed by clinical or pathologic examination; receiving neoadjuvant systemic treatment; regional metastasis in the ipsilateral SCL or IMN area, or distant metastasis; male breast cancer patient; prior history of ipsilateral breast, axilla, or SCL irradiation; prior history of other cancers (excluding thyroid cancer, carcinoma in situ of uterine cervix, and skin cancer); and ductal or lobular carcinoma in situ, phyllodes tumor, or metaplastic tumor diagnosed during pathologic examination of a breast surgical specimen.

### Sample size calculation

The PORT-N1 trial was designed to determine whether the omission of RNI from BCS and PMRT in patients undergoing a mastectomy reduced treatment efficacy. The expected 7-year DFS of the control group in this trial is 90%, based on a previous multicenter retrospective studies conducted by the KROG. The rate of recurrence at 7 years was 12% for the no-PMRT group in KROG 14-23 [20]; the recurrence rate is expected to be lower in the PORT-N1 trial because more than a decade has passed since the previous study. The KROG 14-18 study analyzed pN1 breast cancer patients who underwent anthracycline and taxane chemotherapy, and reported a 5-year DFS of 92.4%, with no difference seen between BCS plus PORT and mastectomy alone groups [21]. Another analysis of KROG 14-18 data compared WBI alone and WBI plus SCL irradiation, and obtained 5-year DFS rates of 94.4 and 92.6%, respectively [19]. The sample size calculation for the PORT-N1 trial assumes a non-inferiority margin of 5%, type I error rate of 5%, 4-year recruitment period, 7-year follow-up, and exponential distribution for time to progression; 134 DFS events are expected, and 525 patients are required for each group for a power of 80%. Assuming a dropout rate of 5%, the final number of patients to be randomized is 1106 (553 for each group).

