**Fig. 3 Fig3:**
[figure not shown]
Example clinical target volumes for post-mastectomy radiotherapy. No post-mastectomy radiotherapy is permitted in the experimental group. Chest wall irradiation with or without regional lymph node irradiation is allowed in the control group

Regular follow-up visits will be scheduled (at 6 months and 12 months, and once per year thereafter) for 7 years after the day of randomization. Performance status, disease status, survival, and adverse events will be recorded at every follow-up visit.

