### Endpoint and statistics

The primary endpoint of this trial is 7-year DFS. The secondary endpoints are locoregional recurrence-free survival (LRFS), distant metastasis-free survival (DMFS), and overall survival (OS). A DFS event is defined as breast cancer recurrence or death. An LRFS event is defined as recurrence in a locoregional area, including the ipsilateral breast/chest wall, axilla, IMN, and SCL area, or breast cancer death. A DMFS event is defined as distant metastasis or breast cancer death. For OS, an event is defined as patient death from any cause. These endpoints will be measured from the date of randomization.

Categorical variables will be compared between the control and experimental groups using the chi-square test, and continuous variables using Student’s *t*-test. DFS, LRFS, DMFS, and OS rates will be calculated by Kaplan–Meier analysis and compared using the log-rank test. The Cox proportional hazards model will be used to evaluate the impact of covariates on clinical endpoints. The threshold for statistical significance is *P* < 0.05. No interim analysis is planned for this trial.

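### The 134 expected DFS events and 80% power fit observation of everyone to year 11, but the visit schedule and the 7-year endpoint give about 105 events; whether power falls short depends on the test scale

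*Protocol article*

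**What the plan says.** All references are to the protocol article.

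- **Sample size calculation.** "The expected 7-year DFS of the control group in this trial is 90"%. The calculation "assumes a non-inferiority margin of 5"%, a "type I error rate of 5"%, and a "4-year recruitment period, 7-year follow-up, and exponential distribution for time to progression". The result is that "134 DFS events are expected, and 525 patients are required for each group for a power of 80"%. A 5% dropout allowance raises 525 to 553 per group, 1106 in total.
- **Study design.** "This trial is anticipated to run for 11 years, with a 4-year recruitment phase and 7-year follow-up".
- **Interventions and follow-up** (the paragraph after the Fig. 3 legend). Visits take place at 6 and 12 months and then yearly, "for 7 years after the day of randomization".
- **Endpoint and statistics.** "The primary endpoint of this trial is 7-year DFS". DFS and the secondary endpoints are to be estimated by Kaplan–Meier and compared with the log-rank test. No interim analysis is planned.

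The article gives no hazard-ratio margin, does not say whether the 5% error rate is one- or two-sided, and describes no follow-up after a participant's seventh year.

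**The concern.** The phrase 7-year follow-up can mean two things. It can be the minimum follow-up, with everyone observed until the last recruit reaches year 7. Early recruits then contribute up to 11 years, and the mean under uniform accrual is 7 + 4/2 = 9 years. Or it can be a fixed 7 years for each participant. The event count fits the first meaning. The visit schedule states the second, and a 7-year DFS rate uses no information from beyond year 7. The 11-year trial duration fits both, so it does not settle the matter.

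At stake is whether the stated event count and power describe the trial as scheduled. If the analysis is a hazard-ratio test and observation stops at 7 years each, the chance of missing a true non-inferiority result rises from the planned 20% to about 28%. With no interim analysis, no planned look at the data would show this before the end.

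**Working it through.** **Inputs.** From the Sample size calculation section: control 7-year DFS 90%, margin 5 points, type I error 5%, 4-year recruitment, exponential times, 525 per group (1050). Assumed: true DFS equal in both arms (only the control rate is given), uniform accrual, and one-sided 5% (the side that reproduces the stated figures).

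**Step 1. Hazard and implied margin.**
- Hazard: λ = −ln(0.90)/7 = 0.01505 per year.
- 90% against 85% implies HR = ln(0.85)/ln(0.90) = 1.5425, so ln HR = 0.4334.

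**Step 2. Reproduce the stated figures.**
- Events required (Schoenfeld): 4 × (1.645 + 0.842)² / 0.4334² = 131.7, so 132. Freedman's formula gives 136. At two-sided 5% these become 168 and 173, which do not match.
- Event probability with 4-year accrual and everyone observed to year 11: 1 − [exp(−7λ) − exp(−11λ)]/(4λ) = 0.1266.
- Expected events: 1050 × 0.12656 = 132.9, against 134 stated.
- Patients per group for 132 events: 132/0.12656/2 = 522; for 134 events, 529. The stated figure is 525.
- Power = Φ(0.4334 × √D/2 − 1.645): D = 132.9 gives 80.3%; D = 134 gives 80.6%.

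The stated design is therefore reproduced closely on this basis.

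**Step 3. Seven years per participant, 90% DFS in both arms, hazard-ratio test.**

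| Patients counted | Events | Power, one-sided 5% |
|---|---|---|
| 1050 | 1050 × 0.10 = 105 | 71.8% |
| 1106 with 5% exponential loss over 7 years | about 108 | 72.8% |
| 1106, no loss | 110.6 | 73.7% |

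The difference from step 2 is 132.9 − 105, about 28 events. At one-sided 2.5%, 105 events would give 60%, and 134 events 71%. Reaching 132 to 134 events within 7 years each would take 660 to 670 per group before dropout.

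**Step 4. Same follow-up, test on the difference in 7-year DFS against 5 points, 525 per group with complete follow-up.**
- SE = √(2 × 0.9 × 0.1/525) = 0.0185.
- One-sided 5%: Φ(0.05/0.0185 − 1.645) = 85%.
- One-sided 2.5%: Φ(0.05/0.0185 − 1.960) = 77%.
- For 80% power this method needs 446 per group (one-sided 5%) or 566 (one-sided 2.5%). Neither is 525, so it does not appear to be the calculation behind the stated size.

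**The case against.** **No loss on the stated endpoint.** The margin is given as 5%, and the abstract says that non-inferiority will be shown by comparing 7-year DFS rates. On that scale 525 per group has 85% power at one-sided 5%, more than claimed. The log-rank test is named for all four time-to-event endpoints alike and is not identified as the non-inferiority test. This stands. A reader might infer that the trial is simply underpowered at 72%, but the article does not support that without a hazard-ratio margin, which it never states.

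**Another route to the event count.** Seven years each with 90% and 85% DFS gives 525 × 0.10 + 525 × 0.15 = 131 events, also close to 134. So the year-11 reading is not the only one that comes near. But 85% is the edge of the margin, where a non-inferiority test succeeds only at its type I error rate and 80% power cannot apply. This route also makes no use of the stated recruitment period. Under equal DFS the count is still 105.

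**A visit schedule is not a censoring rule.** The sentence sets regular visits and does not say that later DFS status is disregarded. The article condenses a fuller protocol, which may fix the cut-off. This stands in part: it cannot be said that the later events will certainly go uncounted. What can be said is that the article gives an event count and a follow-up schedule that do not agree.

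**The trial is not event-driven.** A reader might infer that the sponsor would wait for 134 events and never reach them. Nothing supports that: 134 is an expected number, and reporting is tied to the calendar (after 2033).

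**Conclusion.** The point holds as an inconsistency. The stated 134 events and 80% power agree with observation of all participants to a common year-11 cut-off. They do not agree with 7 years per participant and a 7-year endpoint, which give about 105 events (108 to 111 counting all 1106). That count does not depend on the test scale or the error rate, only on 90% DFS in both arms and 7 years of observation each.

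The effect on power is conditional. It falls to about 72 to 74% on the hazard-ratio scale at one-sided 5%, and is about 85% (one-sided 5%) or 77% (one-sided 2.5%) on the 7-year difference. The hazard-ratio basis and the one-sided 5% are inferred from their agreement with the stated figures, and equal true DFS is the usual planning assumption but is not written.

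**What to change.** Reconcile the Study design, Sample size calculation, Interventions and follow-up, and Endpoint and statistics sections, and state the sidedness of the 5% error rate.

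- **Preferred.** Name the difference in Kaplan-Meier 7-year DFS against 5 points as the non-inferiority test, and restate: about 105 DFS events by year 7; power about 85% at one-sided 5% with 525 per group (77% if one-sided 2.5% is intended). This costs only a change of text.
- **If a hazard-ratio test is kept**, state the margin as a hazard ratio and do one of two things:
  - restate about 105 events and 72% power, again a change of text only; or
  - state that DFS status is collected to a common cut-off when the last participant reaches 7 years (about 133 events, 80%), and make the follow-up schedule agree. The cost is up to four more years of follow-up for those enrolled earliest.

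None of these options needs extra patients.

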### Screening and randomization

Participants will be screened at a radiation oncology department after surgery. After obtaining written informed consent, inclusion and exclusion criteria will be applied based on clinical records, pathologic reports for surgical specimens, and additional history data. Participants who meet the criteria will be enrolled and randomized to the control and experimental groups in a 1:1 ratio. Randomization will be performed by an authorized investigator using a web-based system. The randomization system was devised by the Medical Research Collaborating Center (MRCC) of Seoul National University Hospital and is operated separately from other clinical investigators. Amendment of the randomization process is strictly forbidden by the MRCC. The stratified block randomization method will be used to prepare a randomization table. The stratification factors include surgery type (BCS vs. mastectomy) and histologic subtype (triple-negative vs. non–triple-negative breast cancer). The investigators will submit the screening number, participating institution, date of informed consent, and birthday of the participant to the randomization system to prevent duplicate enrollment. The participants and investigators are not blinded to the randomization results, and the participant may be informed of the precise details and field settings of the radiotherapy. After group allocation is confirmed, the written consent form will be printed and stored with the clinical trial documents.

### Interventions and follow-up

There are no precise requirements for surgical and adjuvant systemic therapy; participants will be treated based on institutional preference, except in the case of radiotherapy. Genomic testing to determine suitability for adjuvant chemotherapy is optional. For PORT, a photon beam of 4–10 MV is recommended. Both three-dimensional conformal radiation therapy and intensity-modulated radiation therapy are permitted for radiotherapy planning and beam delivery. An electron beam can be applied for IMN and tumor bed boost irradiation. Computed tomography-based simulation is required for all participants. Both hypofractionated and standard dose-fractionation schemes are allowed. Hypofractionated regimens are defined as those with a dose per fraction of 2.5–3.0 Gy, dose to the whole breast or chest wall of 39–45.9 Gy, and 13–17 fractions. Standard fractionation regimens are those with a dose per fraction of 1.8–2.0 Gy, dose to whole breast or chest wall of 45–50.4 Gy, and 23–28 fractions. There are no restrictions in terms of the tumor bed boost irradiation technique or dose fractionation scheme.

The clinical target volume (CTV) should be delineated based on Radiation Therapy Oncology Group (RTOG) [22] or EORTC guidelines [23, 24]. In control group participants who underwent BCS, the whole breast and regional lymph node area should be irradiated. The regional radiation field should be a “high-tangent” (upper margin ≤2 cm inferior to the humeral head, to encompass axillary levels I and II) or wider field. The SCL and IMN areas can be irradiated in the control group. Examples of CTV delineation for PORT after BCS in both groups are shown in Fig. 2. In participants who underwent mastectomy, the chest wall should be irradiated with or without inclusion of the regional lymph node area. In the experimental group, WBI alone (without RNI) will be performed in participants who underwent BCS, and the CTV should be delineated accordingly. No irradiation will be delivered to patients in the experimental group who underwent mastectomy. Examples CTVs for PMRT are shown in Fig. 3. Implant-saving target delineation is allowed, based on published guidelines [25].

